#### eGFR

Data will be listed and summarized for ESRD subjects on standard hemodialysis, ESRD subjects on hemodiafiltration, subjects with normal renal function matched to ESRD subjects on standard hemodialysis, and subjects with normal renal function matched to ESRD subjects on hemodiafiltration for the safety and the PK population, if different.

 Section updated via Amendment 2 to clarify the enrollment of subjects on standard hemodialysis and hemodiafiltration

|  |  |                                                                                             |
|--|--|---------------------------------------------------------------------------------------------|
|  |  | CRS Study No.: 090/18-03.MT
Sponsor Study No.: AT1001-035
EudraCT No.: 2018-003684-57 |
|--|--|---------------------------------------------------------------------------------------------|

#### 9.7.1.4 Pharmacokinetics

##### Plasma concentrations

Individual concentrations of migalastat in plasma will be displayed graphically and listed on the original as well as on a logarithmic scale.

For descriptive statistics of plasma migalastat concentrations, values below lower limit of quantification (LLOQ) will be assigned a value of 0. Descriptive statistics of concentrations will be calculated if at least 1/2 of the individual data points have been measured equal or above LLOQ.

Individual data points in the lag-time between time zero and the first quantifiable concentration will be displayed as 0 on the linear concentration scale and they will not be displayed on the logarithmic scale.

##### Urine concentrations

Individual concentrations of migalastat in urine will be listed and summarized with descriptive statistics. Figures will be provided by group.

##### Dialysate concentrations

Individual concentrations of migalastat in dialysate will be listed and summarized with descriptive statistics. Figures will be provided by group.

##### Pharmacokinetic characteristics in plasma

Calculation of the PK characteristics will be based on actual blood sampling times [h] (relative to the corresponding administration time) rounded to 2 decimal digits and negative pre-dose times set to zero.

For calculation of the PK parameters the following rules will be applied: At time points in the lag-time between time zero and the first quantifiable concentration, concentrations below LLOQ will be calculated as zero. Concentrations below LLOQ between 2 quantifiable concentrations will be set to missing. Trailing concentrations below LLOQ will set to missing.

Descriptive statistics of PK parameters will be calculated.

For  $t_{\max}$  frequency tables will be drawn based on the nominal time of  $t_{\max}$ .

Figures will be provided.

Individual data points in the lag-time between time zero and the first quantifiable concentration will be displayed as 0 on the linear concentration scale and they will not be displayed on the logarithmic scale.

##### *Correlation with eGFR*

eGFR values (x-axis) will be plotted against the respective main PK parameters (y-axis).

|  |  |                                                                                             |
|--|--|---------------------------------------------------------------------------------------------|
|  |  | CRS Study No.: 090/18-03.MT
Sponsor Study No.: AT1001-035
EudraCT No.: 2018-003684-57 |
|--|--|---------------------------------------------------------------------------------------------|

#### Pharmacokinetic characteristics in urine and dialysate

Urine and dialysate PK will be based on concentrations and volumes.

Figures will be provided.

#### Comparisons

For the group of ESRD subjects under hemodialysis it is an intra-individual situation. Each subject serves as his own control (with versus without dialysis). Tables will display the individual data paired for each subject.

The comparison of ESRD subjects with healthy subjects will be handled as an intra-individual situation as well, because the subjects match for demographic characteristics. However, display of characteristics (PK and others) will be given both, inter- and intra-individually.

### **9.7.1.5 Safety and tolerability**

Results of all safety measurements will be listed individually and, as appropriate, summarized.

#### Adverse events

All AEs will be listed together with information on onset, duration, severity, seriousness, relationship to the IMP, outcome and action taken.

Adverse events will be coded using MedDRA. Coding will be performed with the dictionary versions currently used by CRS-Mannheim at time point of study start. Dictionaries will not be changed during the study. Coding terms and investigator terms will be given in the listings.

An AE will be referred to the treatment and time point after which it occurred, i.e. any AE occurring before (first) dosing will be counted as baseline complaint/ pre-treatment AE and an event will only be considered as treatment-emergent adverse event (TEAE) if occurring after or at (first) dosing.

Only TEAEs will be analyzed using summary tables. Frequency tables for TEAEs will be given by system organ class and preferred term and will be provided by severity and relationship to IMP.

#### Other safety assessments

Descriptive statistics will be calculated for laboratory parameters, vital signs including body temperature, and ECG parameters. Changes from baseline will be summarized. Data outside the reference ranges will be flagged in the listings with 'L' for low and 'H' for high. Information on clinical significance as assessed by an investigator will also be provided in the listings. Additional tables with the number of all abnormal values will be provided for safety laboratory parameters. A separate table will show all abnormal results.

Physical examination findings will be listed.

|  |  |                    |                |
|--|--|--------------------|----------------|
|  |  | CRS Study No.:     | 090/18-03.MT   |
|  |  | Sponsor Study No.: | AT1001-035     |
|  |  | EudraCT No.:       | 2018-003684-57 |

#### 9.7.1.6 Level of significance

There are no inference statistical analyses. If, with descriptive explorative intention, confidence intervals are calculated, the 95% limits will be presented for differences between groups and the 90% limits for questions of (bio-)equivalence.

#### 9.7.1.7 Procedures in case of missing, unused, and spurious data

In general, missing data will not be replaced or imputed in any way. Only for PK concentrations the rules mentioned above are applied.

For calculation of onset and duration of an AE the following worst case rules will be applied:

- In case of incomplete onset date or onset time the missing information will be imputed such that the onset date or time is minimal [e.g. Onset of AE (date and time): 01JAN2012, 09:UNK h is set to 01JAN2012, 09:00 for calculation of onset and duration].
- In case of incomplete end date or end time the missing information will be imputed such that the duration is maximal [e.g. Onset of AE (date and time): 01JAN2012, 08:00; end of AE (date and time): 01JAN2012, 09:UNK h is set to 01 January 2012, 09:59 for calculation of duration].

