Adverse events that begin or pre-existing conditions that worsen after the first dose of study drug will be considered TEAEs.

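### The rule that sets an incomplete AE onset to its earliest possible value is worst case for duration but anti-conservative for deciding whether the event is treatment-emergent

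*Protocol*

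**What the plan says.** Section 9.7.1.7 opens its AE rules with "For calculation of onset and duration of an AE the following worst case rules will be applied". For onset the rule is "In case of incomplete onset date or onset time the missing information will be imputed such that the onset date or time is minimal"; for the end, the missing part is chosen to make duration longest. Its onset example is a missing minute.

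The Adverse events part of Section 9.7.1.5 draws the line between pre-treatment and treatment-emergent events. On one side, "any AE occurring before (first) dosing will be counted as baseline complaint/ pre-treatment AE"; on the other, "an event will only be considered as treatment-emergent adverse event (TEAE) if occurring after or at (first) dosing". Section 19.1.1 agrees in substance: "Adverse events that begin or pre-existing conditions that worsen after the first dose of study drug will be considered TEAEs".

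For reporting, Section 9.7.1.5 says "Only TEAEs will be analyzed using summary tables", and also "All AEs will be listed together with information on onset, duration, severity, seriousness". For subjects with more than one dose it adds: "An AE will be referred to the treatment and time point after which it occurred".

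The protocol gives no exception for onset on a dosing day and no separate imputation rule for the TEAE flag.

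**The concern.** The earliest possible onset gives the longest duration, so for duration the rule is conservative. Treatment emergence works the other way. Moving an onset earlier can turn a post-dose event into a pre-dose one, never the reverse. A rule labelled worst case can therefore only lower the TEAE count.

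TEAEs are the first-listed secondary endpoint and serve the safety and tolerability objective. Summaries are grouped into four sets of 3 planned subjects (two dialysis methods and their matched controls), so one event lost from a table is visible in the percentages.

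**Working it through.** **Inputs**
- Onset rule: Section 9.7.1.7.
- TEAE definition and tabulation: Section 9.7.1.5.
- Dosing after an overnight fast: Section 9.4.5. The dose is therefore taken to follow 00:00 on Day 1. No clock time is given; I assume 07:00 to 10:00.
- Planned subjects: 6 ESRD (3 + 3) with two doses and 6 controls with one (Sections 9.1 and 9.4.1).

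**The plan's own examples.** Missing hour or minute set to 00: 09:UNK becomes 09:00, as in Section 9.7.1.7. For the end, onset 08:00 and end 09:UNK gives an end of 09:59 and a duration of 119 minutes. Both reproduce, and both behave as intended for duration.

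**The same onset rule put through the TEAE definition**

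| Recorded onset | Imputed onset | Result |
|---|---|---|
| First dosing day, time unknown | 00:00 | Pre-treatment at every assumed dosing time |
| First dosing day, 08:UNK, dose 08:10 | 08:00 | Pre-treatment |
| First dosing day, 08:UNK, dose 08:00 | 08:00 | TEAE (at dosing) |
| First dosing day, hour after the dosing hour | Start of that hour | TEAE |
| Period 2 dosing day (ESRD), time unknown | 00:00 | TEAE, but referred to the Period 1 dose |

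A date with only the day missing becomes the first of that month. If that falls before the first dose, the event is again pre-treatment; if it falls after, the event remains a TEAE.

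**How much of the first dosing day lies after the dose.** Share = (24 − dosing hour)/24. At 07:00 it is 17/24 = 71%; at 10:00 it is 14/24 = 58%. The rule assigns an unknown time to the shorter, pre-dose part of the day at every dosing time tried.

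**Where it applies.** Planned dosing days = 6 × 2 + 6 × 1 = 18. Of these, 12 are first-dose days, where an event can be lost from the tables. The other 6 are Period 2 days, where it can only be misattributed.

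**Effect of one lost subject on incidence:** 1/3 = 33 points, 1/6 = 17 points, 1/12 = 8 points. These are upper limits. They apply only if the subject has no other TEAE (or, for a single preferred term, no other event in that term).

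**The case against.** The strongest reply is that Section 9.7.1.7 does not say that the imputed value sets the TEAE flag. Section 9.7.1.1 describes the statistical sections as an overview and leaves details to a SAP, which is not at hand and could contain a separate flag rule. This stands as a limit on certainty: the link is inferred. The inference is strong, though. The rule covers the calculation of onset and not only duration, the flag depends on onset relative to dosing, and no other onset rule is given. Nor is this a detail merely left for later, because the protocol states a rule and calls it worst case.

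The second reply is that the trigger is rare. Subjects are in-house from the evening of Day -1 to the morning of Day 3, AEs are collected on Day -1 and Day 1, and vital signs are taken before the dose and at 1, 2, 4, 6 and 12 h after it. This stands. ESRD subjects do leave the centre for dialysis, but on Day 2 in Period 1 and on Day 1 only in Period 2. That absence therefore bears on attribution and not on loss from the tables.

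Third, nothing disappears from the report. Every AE is listed, and with 12 subjects and a descriptive analysis the listing can be read in full. SAE reporting does not use the flag, and a data review meeting precedes database lock. This also stands.

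A reader might infer more: that an AE of unknown time on any dosing day leaves every TEAE table. The documents do not support that. On the 6 Period 2 dosing days, 00:00 is still after first dosing, so the event remains a TEAE. The protocol also does not say that TEAEs will be tabulated by period, so the shift to Period 1 may affect attribution without changing a planned table.

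**Conclusion.** The point holds in a limited form. For onsets on the first dosing day that fit both before and after the dose, and for partial dates imputed to before the first dose, the stated rule classes the event as pre-treatment and removes it from the TEAE tables but not from the listing. On the Period 2 dosing day the event is credited to Period 1. The direction is certain: the rule cannot raise the TEAE count.

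The size depends on how often onsets are incomplete. The protocol gives no frequency, and in-house observation suggests few. The limits of 33, 17 and 8 points are conditional on one such subject with no other TEAE; they are not expected effects. The conclusion rests on two assumptions: that the imputed onset feeds the TEAE flag, and that dosing comes after midnight. The correction is worth making because it is cheap and the present rule is conservative for only one of its two uses.

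**What to change.** Keep minimal onset for duration only, and add to Section 9.7.1.7:

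> For the TEAE flag, an AE with incomplete onset is treatment-emergent unless the known parts of its onset or end show that it began before the first dose. If the known parts of the onset fit both before and after a dose on that dosing day, the AE is referred to that day's dose. If the date is too incomplete to identify the period, the AE is counted as a TEAE and its period is shown as undetermined.

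Onsets whose known part already shows that they follow the dose stay as they are. With a dose at 08:30 (for illustration), 14:UNK is plainly post-dose and must not be moved to the dosing time. A broader rule that set every onset not proved pre-dose to the time of dosing would make that error, and would leave the dose undefined for a two-dose subject with a wholly missing date.

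The cost is three sentences in the protocol or SAP. The downside is that a few true pre-dose events may be counted as TEAEs, which is the conservative direction for a safety summary.

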#### 9.7.1.8 Interim analysis

An interim statistical analysis will not be performed.

#### 9.7.2 Determination of sample size - amended

The planned sample size of 6 evaluable subjects per renal function group (in the ESRD group on hemodialysis: 3 subjects on standard hemodialysis, 3 subjects on hemodiafiltration) is not based on a power calculation, but is judged based on experience to be adequate to obtain reliable results meeting the objectives of this study.

### 10 Data handling and record keeping

#### 10.1 Case report forms and recording of data

##### 10.1.1 Electronic records

Electronic records are defined as any combination of text, graphics, data, audio, pictorial, or other information represented in digital form that is created, modified, maintained, archived, retrieved or distributed by a computer system. An eCRF is an auditable electronic record of information that generally is reported to the sponsor on each study subject according to the clinical investigation protocol.

 Statement added via Amendment 2  
Integrated Clinical Study Protocol, Final 3.0, 29 Aug 2019

|  |  |                    |                |
|--|--|--------------------|----------------|
|  |  | CRS Study No.:     | 090/18-03.MT   |
|  |  | Sponsor Study No.: | AT1001-035     |
|  |  | EudraCT No.:       | 2018-003684-57 |

## 10.2 Data collection (eCRF)

Data will be collected using an eCRF system that is specifically designed for this study. The data collected will be captured in an eCRF system that meets the technical requirements described in 21 CFR part 11. The eCRF system will be fully validated to ensure that it meets the scientific, regulatory, and logistical requirements of the study before it is used to capture data from this study. Before using, all users will receive training on the system and any study specific training. After they are trained, users will be provided with individual system access rights.

Data will be collected at the investigational center by appropriately designated and trained personnel. The eCRF pages must be completed for at least each dosed subject according to the data source. Subject identity should not be discernible from the data provided on the eCRF. Data will be verified using the data source by the study monitor, and reviewed for consistency by Data Management using both automated logical checks and manual review. All data collected will be approved by the investigator at the investigational center. This approval acknowledges the investigator's review and acceptance of the data as being complete and accurate.

All other Data Management relevant issues will be described within a Data Management Plan.

## 10.3 Data quality assurance

Clinical Data Management is responsible for the accuracy, quality, completeness, and internal consistency of the data from this study. Data handling, including data quality assurance, will comply with international regulatory guidelines, including ICH GCP guidelines. Data management and control processes specific to this study, along with all steps and actions taken regarding data management and data quality assurance, will be described in a Data Management Plan.

Electronic case report forms will be processed and reviewed for completeness, consistency, and the presence of mandatory values. Applicable terms will be coded according to the coding conventions for this study. Logical checks will be implemented to ensure data quality and accuracy.

Any necessary changes will be made in the clinical database, and data review and validation procedures will be repeated as needed. Data from external sources will be compared with the information available in the eCRF. Discrepancies found will be queried.

At the conclusion of the study, the eCRF and all other study data will be locked to further additions or corrections. Locking the study data represents the acknowledgement that all data have been captured and confirmed as accurate.

### 10.3.1 Archiving of data and data retention

The archiving period of study-related data (see essential documents, Section 8 of the Note for Guidance on Good Clinical Practice) is based on the requirements of the

|  |  |                                                                                                                  |
|--|--|------------------------------------------------------------------------------------------------------------------|
|  |  | CRS Study No.: 090/18-03.MT
Sponsor Study No.: AT1001-035
EudraCT No.: 2018-003684-57 |
|--|--|------------------------------------------------------------------------------------------------------------------|

"Allgemeine Verwaltungsvorschrift zur Anwendung der Arzneimittelprüfrichtlinien" and the Note for Guidance on Good Clinical Practice.

According to this, sponsor must arrange for essential clinical study documents (including case report forms) other than subject's medical files, to be kept by the owners of the data (e.g., sponsor, investigator).

Subject's medical files should be retained in accordance with applicable legislation and in accordance with the maximum period of time permitted by the clinic, institution or private practice.

The investigator/institution should take measures to prevent accidental or premature destruction of these documents.

The sponsor can require documents to be retained for a longer period of time. It is the responsibility of the sponsor to inform the clinic, institution (CRS) or practice in writing as to when these documents no longer need to be retained.

Nevertheless, before destruction of the respective documents (e.g. source data) in addition the managing directors of CRS have to be consulted.

### **10.3.2 Data access**

The sponsor has to ensure that data collected are complete, accurate, reliable and consistent. Data changes should be recorded in a way that there is no possibility to delete or change data without tracking, i.e., the original data should be retrievable. Security systems will be in place to prevent unauthorized access to the data.

Each study site must maintain a list of individuals who are allowed to enter or change data. This list has to be filed in the investigator site file.

## **11 Quality assurance and quality control, audits, and inspections**

### **11.1 Quality control and quality assurance**

The sponsor is responsible for implementing and maintaining quality assurance and quality control systems with written SOPs to ensure that studies are conducted and data are generated, documented (recorded), and reported in compliance with the protocol, GCP, and the applicable regulatory requirements.

The sponsor is responsible for securing agreement from all involved parties to ensure direct access to all study related sites, source data/documents, and reports for the purpose of monitoring and auditing by the sponsor, and inspection by domestic and foreign regulatory authorities [GCP].

Quality control should be applied to each stage of data handling to ensure that all data are reliable and have been processed correctly [GCP].

|  |  |                    |                |
|--|--|--------------------|----------------|
|  |  | CRS Study No.:     | 090/18-03.MT   |
|  |  | Sponsor Study No.: | AT1001-035     |
|  |  | EudraCT No.:       | 2018-003684-57 |

Agreements, made by the sponsor with the investigator/institution and any other parties involved with the clinical study, should be in writing, as part of the protocol or in a separate agreement [GCP].

## 11.2 Audit

Study related activities and documents may be audited according to the respective audit plan to determine if performance and evaluation of the study were compliant with the protocol, SOPs, GCP and the applicable regulatory requirements. Audits will be performed by auditors who are independent from the clinical study and its conduct.

The investigator will permit the auditors access to the facilities and documents at agreed times.

## 11.3 Inspection

Regulatory authorities may conduct an official review of all study documents, facilities, records and other material related to the study.

The investigator must cooperate with any inspection.

The subjects will agree with signing the informed consent to the direct access of their data for study -related monitoring, audit, IEC review, and regulatory inspection.

## 12 Confidentiality of subject data

All clinical information will be recorded, processed, handled, and stored by the sponsor and investigator in such a way that it can be accurately reported, interpreted and verified while the confidentiality of records and the personal data of the subjects remain protected in accordance with the applicable law on data protection.

All parties being involved in recording and processing of study related personal data will implement appropriate technical and organizational measures to protect information and personal data against unauthorized or unlawful access, disclosure, dissemination, alteration, or destruction or accidental loss, in particular where the processing involves transmission over a network.

Where processing of personal data is carried out on behalf of the sponsor, the sponsor will use only processors providing sufficient guarantees to implement appropriate technical and organizational measures in such a manner that processing will meet the requirements of the applicable European law on data protection. This will be governed by a written contract.

All study related records and data of the subjects which will be transferred to the sponsor or regulatory authorities will be pseudonymized.

The investigator ensures that any documents or data disclosed to the sponsor do not contain any information disclosing the identity of the subject.

|  |  |                                                                                             |
|--|--|---------------------------------------------------------------------------------------------|
|  |  | CRS Study No.: 090/18-03.MT
Sponsor Study No.: AT1001-035
EudraCT No.: 2018-003684-57 |
|--|--|---------------------------------------------------------------------------------------------|

